### Future Implications

This study addresses the public health problem by optimizing a technology-driven, tailored approach that can operate in low-resource environments with unlimited users to prevent falls and reduce health disparities in low-income older adults. It also supports using the results to tailor interventions to improve PA and reduce falls [31,51,52]. If effective, this intervention can provide an innovative, scalable, and accessible model for fall prevention in diverse and underserved populations. The use of a noninvasive technology that does not require special training and can operate in low-resource environments may scale up the intervention for low-income communities. The BBS can be used for fall risk assessment, tailored interventions, and tracking the changes in balance performance. Technology-based physio-feedback regarding balance has a positive effect on balance confidence and task selection, which could help reframe unrealistic perceptions and lead to healthy behaviors. This study is conducted by an interdisciplinary team and collaborates with community-based and public health organizations, which will ensure the research is relevant, contextually appropriate, and will ultimately be translated into real-world settings.

### Limitations, Potential Challenges, and Alternatives

There are several limitations and potential challenges including (1) recruitment and retention, (2) respondent burden, (3) staffing, and (4) lack of skills to use BBS technology.

#### Recruitment and Retention

Although the recruitment and retention of low-income older adults in randomized controlled trial studies is often challenging, our tailored strategies will address these issues by ensuring that our bilingual RAs are well trained, providing information in English and Spanish versions, and using a straightforward data collection process.

#### Respondent Burden

During the intervention, the PCs and RAs will complete a weekly exercise log and monthly fall or near falls logs. After the 8-week intervention, the only data to be collected monthly from participants will be the fall logs. These were used successfully in our pilot study; we found no falls and 2 near falls in the PEER group.

#### Staffing

Our staffing plan ensures coverage by study personnel for 8 weeks of the intervention and the 3- and 6-month follow-up assessment.

#### Lack of Skills to Use BBS Technology

This study does not expect low-income older adults to test themselves using the BBS. We will train an RA at each site to run the test.

### Conclusions

More than half of all older adults have maladaptive FRA, leading to reduced PA and a corresponding increased risk of falls. This study focuses on fall interventions tailored to low-income older adults who have a mismatch between physiological fall risk (body) and perceived fall risk (mind). The PEER is a novel intervention that combines concepts of physio-feedback, cognitive reframing, and peer-led exercise by motivating a shift in self-estimation of fall risk to align with physiological fall risk to improve balance, PA, and negative aging self-perception that no one has studied before. The major strength of this study is the use of a noninvasive technology that does not require special training and can operate in low-resource environments with unlimited users. The PEER intervention can be implemented on a large scale in community settings. Such an approach may reach older individuals at risk who do not participate in or are not referred to standardized conventional training programs to help them prevent falls and reduce health disparities.

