Addressing maladaptive fall risk appraisal (FRA) can be challenging owing to self-report bias and cognitive deficit. We developed an *FRA matrix*, a graphical grid categorizing perception (levels of FOF) and body function (level of balance) into four groups: (1) rational FRA (low FOF and normal balance), (2) incongruent FRA (low FOF despite poor balance), (3) irrational FRA (high FOF despite normal balance), and (4) congruent FRA (high FOF and poor balance) [22,23]. On the basis of our previous works [24-26] and other studies [27], approximately 64% to 79% of older adults had maladaptive FRA. Older adults in maladaptive FRA groups were 2 to 3 times more likely to fall than those in adaptive FRA [24,25]. Those with irrational FRA serve as a barrier, creating a high FOF that inhibits low-income older adults from staying physically active. High FOF restricts mobility and daily activities and increases fall risk [28], with chronic FOF predicting an increased risk of functional decline [16]. Individuals with FOF overestimated their gait performance and showed deficits in motor imagery of gait [29]. They may not exhibit increased FOF and subsequently fall if they accurately appraise their physical abilities [27]. Evidence, including our data, indicates that an intervention program must help older adults reframe FRA and maintain PA [27,30]. We found that the FRA matrix is associated with moderate to vigorous PA (MVPA), Centers for Disease Control and Prevention (CDC) fall risk score, self-reported strength and flexibility, difficulty walking several city blocks, and left-hand average handgrip strength [31].

Older adults with FOF overestimated their gait performance and showed deficits in motor imagery of gait [29]. Older adults may exhibit less FOF and subsequently fall if they accurately appraise their physical abilities [27]. In addition, maladaptive FRA can result in activity withdrawal, decline in physical and cognitive abilities, and increased social isolation [23]. Therefore, adaptive FRA is a key component of activity participation and maintenance of self-reliance [32]. Several types of interventions focus on reducing FOF [33-41]; however, some degree of FOF can increase conscious awareness and reduce fall risk by encouraging individuals to avoid exposure to unnecessary risks [42]. Low-income older adults with better-perceived physical health may experience less FOF [43].

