In addition, existing fall prevention intervention technologies do not enable participants and practitioners to interact and collaborate [44] even with technologies that bring viable strategies to maintain independence, prevent disability, and increase access to quality care. Acceptability, privacy issues, technology costs, implementation costs, and barriers have rarely been addressed [44]. Research is also limited on the use of technology to enhance motivation and help individuals align their perception with physiological fall risk [45]. Offering additional advantages, technology-based exercise interventions have good adherence and may provide a sustainable method of promoting PA and preventing falls [45,46].

We developed a novel, 8-week Physio-Feedback Exercise Program (PEER) [32], which includes (1) technology-based physio-feedback using a real-time portable innovative technology—the BTrackS Balance Tracking System (BBS), which is reliable [47,48] and affordable, allows for home testing, provides feedback, and tracks balance progression; (2) cognitive reframing [49] using the FRA matrix; and (3) peer-led exercises [50] focusing on balance, strength training, and incorporating exercises into daily activities. Our pilot study supports the feasibility and acceptability of using BBS technology in low-income communities to screen individuals with maladaptive FRA. It also supports using the results to tailor interventions to improve PA and reduce falls [31,51,52]. The findings highlight reducing sedentary time to help shift from irrational to rational groups and increasing MVPA time to help shift from congruent and irrational to rational FRA groups. We found a significant difference in sedentary time between the rational and irrational groups (*P*=.04). This indicates that if a person exhibits high FOF despite their normal balance (irrational), they tend to be more sedentary compared with people with low FOF and normal balance (rational). Importantly, we showed that the FRA matrix and 4-group quadrant design (irrational, incongruent, congruent, and rational) allows stratified analysis, which provides a more efficient overall fall risk assessment, which has rarely been reported in the literature.

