### Aims and Hypotheses

Aim 1 is to examine the effects of the technology-based PEER intervention on fall risk, dynamic balance, and accelerometer-based PA.

The hypotheses are as follows:

*H 1.1:* The PEER group will reduce the fall risk compared with the control group.*H 1.2:* The PEER group will improve the dynamic balance compared with the control group.*H 1.3:* The PEER group will improve accelerometer-based PA compared with the control group.

Aim 2 is to examine the effects of the PEER intervention on FRA shifting and negative self-perceptions of aging.

The hypotheses are as follows:

*H 2.1:* The PEER group will have a more adaptive shifting compared with the control group.*H 2.2:* The PEER group will have a more positive shift in their perceptions of aging compared with the control group.

Aim 3 is to explore participants’ experiences with the PEER intervention and potential barriers to access and adoption of the technology-based PEER intervention to inform future research. A purposive sample of 30 participants from the PEER group will participate in semistructured one-on-one interviews to explore their perceptions of barriers to access and adoption of technology and intervention.

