### Study Participants

A sample of 340 participants will be enrolled if they meet all the following inclusion criteria:(1) aged ≥60 years, (2) cognitively intact based on Mini-Mental State Examination score ≥24 [55], and (3) able to stand without assistance. Exclusion criteria were as follows: (1) a medical condition precluding exercise and PA, such as feeling pressure when performing PA; (2) currently receiving treatment from a rehabilitation facility; (3) plan to move within 1 year; (4) hospitalized >3 times in the past 12 months; and (5) does not speak English or Spanish.

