#### Step 2: Cognitive Reframing

*Cognitive reframing* will be based on the FRA matrix. We will present the FRA matrix, and activities will be tailored based on the quadrant that the participant fits (Figure 1):

*Quadrant 1* (irrational): focus on increasing balance confidence and maintaining exercise.*Quadrant 2* (incongruent): focus on individual fall risk factors from the CDC fall risk checklist, enhance fall risk awareness, and participate in the exercise.*Quadrant 3* (congruent): focus on individual fall risk factors from the CDC fall checklist and participate in the exercise.*Quadrant 4* (rational): encourage to maintain exercise.

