Raw acceleration data from ActiGraph will be downloaded and converted to “.csv” files using ActiLife 6 Software (version 6.13.4; ActiGraph LLC). PA data will be processed using the R package *GGIR* (version 2.4-0). *GGIR* R package used to process multiday raw accelerometer data for PA research [103] includes (1) auto-calibration of acceleration signals according to local gravity [104], (2) detection of nonwear time, and (3) calculation of the average magnitude of dynamic acceleration corrected for gravity (ie, Euclidean Norm Minus One) over 5-second epochs and expressed in milli-gravitational units (mg) [105]. Nonwear time and sustained abnormally high accelerations will be imputed using the default settings [105]. The Euclidean Norm Minus One cut-off points will be used to estimate the total time spent in sedentary behavior, light intensity PA, and MVPA in participants.

For missing data treatment, the missing values will be imputed using the method of multiple imputations [106]. The maximum number of missing values within a scale will be based on the guidelines provided by the scale developers or based on a limit of 25% missing values. In the first analysis, all low-income older adults will be included according to their original group assignment [100]. Participants in the PEER group who completed at least 5 of the 8 group-based sessions will be included in the per-protocol analysis. Although every attempt will be made to ensure that low-income older adults complete all assessments, there may be some participant attrition over time. The missing data mechanism is assumed to be missing at random. The dropout patterns or missing data rates for the 2 arms will be examined to assess the differences. When possible, the models should be modified to account for relevant factors such as age, sex, general health perception, and the number of falls in the 6 months leading up to the baseline. To determine the impact of the PEER intervention during follow-up evaluations, the group-by-time interaction term will be incorporated into the model. Effect sizes (Cohen *d*) [107,108] will be calculated based on the estimated means and the pooled SD.

Aim 2 is to examine the effects of the intervention on FRA shifting and negative self-perceptions of aging.

The hypotheses are as follows:

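### Baseline FRA quadrant is not named as an adjuster, which matters most in the adaptive-shifting model, and the Conclusions describe a narrower group than the trial enrols

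*Protocol article*

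**What the plan says.** **Stated focus.** The Conclusions say: "This study focuses on fall interventions tailored to low-income older adults who have a mismatch between physiological fall risk (body". By the definitions in Background and FRA Shifting, a mismatch means the irrational quadrant (high fear of falling, normal balance) or the incongruent quadrant (low fear, poor balance). The rational and congruent quadrants have no mismatch.

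**Population.** The Aims section sets no FRA limit: "Aim 1 is to examine the effects of the technology-based PEER intervention on fall risk, dynamic balance, and accelerometer-based PA". Study Participants reads "A sample of 340 participants will be enrolled if they meet all the following inclusion criteria", and the criteria are "1) aged ≥60 years, (2) cognitively intact based on Mini-Mental State Examination score ≥24 [55], and (3) able to stand without assistance". No inclusion or exclusion criterion uses fear of falling, the BBS score or the quadrant.

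**Role given to the quadrant.** Background reports that the FRA matrix is associated with MVPA and the CDC fall risk score, and says that the four-quadrant design "allows stratified analysis, which provides a more efficient overall fall risk assessment". Step 2: Cognitive Reframing varies the content by quadrant; for the fourth the entry is "rational): encourage to maintain exercise". Both component scores, BBS and short FES-I, are taken at T1.

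**Models (Data Analysis).** Aim 1 uses a linear mixed model over T1 to T4 with a group-by-time term. On covariates, "the models should be modified to account for relevant factors such as age, sex, general health perception", plus falls in the six months before baseline. H2.1 uses a binomial mixed model for repeated shifting status, and no baseline covariate is named for it.

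**The concern.** The article treats baseline quadrant as prognostic and lets it decide what participants receive, yet neither model description names it. For H2.1 it also largely determines how far a participant has to move to count as a success. If the arms differ in starting quadrant, an unadjusted comparison of adaptive shifting mixes that difference with the effect of PEER.

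Such a difference is easy to get here. Six sites are planned, three per arm, and participants are recruited after the site allocation has been made.

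The sentence in the Conclusions adds a problem of wording: it names a narrower group than the one whose effect Aim 1 will estimate.

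**Working it through.** The point disputes no figure in the plan. It rests mainly on reading the passages together; arithmetic is needed only for the cost of an analysis by mismatch status.

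**1. Distance to the rational quadrant (FRA Shifting).** Rational requires short FES-I ≤10 and BBS ≤30.

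| Start | Short FES-I | BBS | Cut-offs to cross |
|---|---|---|---|
| Irrational | >10 | ≤30 | one (fear) |
| Incongruent | ≤10 | >30 | one (balance) |
| Congruent | >10 | >30 | both |

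The H2.1 denominator pools all three.

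**2. What imbalance does to H2.1.** Let r_q be the chance of adaptive shifting from quadrant q with no PEER effect, and w_q the share of an arm's non-rational starters in q. The crude difference between arms is then Σ (w_q,PEER − w_q,control) × r_q. It is zero only if the weights agree, the r_q agree, or the differences cancel. Step 1 gives a reason for the r_q to differ. The article gives neither quadrant shares nor quadrant-specific shift rates, so the size cannot be calculated.

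**3. Aim 1.** The same covariate helps less. T1 is one of the four measurements in the outcome vector and the effect is read from group-by-time, so stable differences in level between quadrants are already largely accounted for. What remains is any link between quadrant and change.

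**4. Cost of an Aim 1 contrast by mismatch status.** With n per arm, SD σ and share p in the mismatch group:
- Pooled SE = σ√(2/n).
- SE in the mismatch group alone = σ√(2/(np)), a ratio of 1/√p.
- SE of the difference between the two groups' effects = σ√(2/(np) + 2/(n(1−p))), a ratio of 1/√(p(1−p)).

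The only share available is from Background: "approximately 64% to 79% of older adults had maladaptive FRA". It is a stand-in, because maladaptive FRA is not defined by quadrant in the article.

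| p | Group alone, 1/√p | Contrast, 1/√(p(1−p)) |
|---|---|---|
| 0.64 | 1.25 | 1/0.480 = 2.08 |
| 0.79 | 1.13 | 1/0.407 = 2.46 |

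Since p(1−p) is at most 0.25, the contrast ratio is at least 2 whatever the true share.

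**5. Illustrative power of that contrast.** The plan's secondary-outcome statement (120 per arm, d=0.36, 80% power) reproduces within two patients: 122 per arm, or 79.6% power at 120. An effect that an 80%-power pooled test would detect has noncentrality 1.96 + 0.84 = 2.80. If the contrast were as large as that effect, its power would be Φ(2.80 × 0.480 − 1.96) = Φ(−0.62) = 27% at p = 0.64 and Φ(2.80 × 0.407 − 1.96) = Φ(−0.82) = 21% at p = 0.79. Clustering by site is ignored throughout and would lower precision further.

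**The case against.** The strongest reply is that nothing is wrong. Aims, eligibility and the Aim 1 model all concern low-income older adults in general and agree with one another. The covariate list is open-ended, and a statistical analysis plan that is not shown could add the quadrant. The sentence in the Conclusions says whom the intervention is tailored to and defines no estimand. Most of this stands. It leaves a recommended improvement rather than an error: where the article lists its adjusters, it leaves out one that its own background marks as prognostic.

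A reader might infer more: that the trial fails to estimate the effect in its own target group, and that the pooled effect is diluted by people with nothing to correct. The documents do not support this.
- H2.1 does condition on starting quadrant, although its denominator adds the congruent group, which has no mismatch.
- Rational starters have their own outcome, maladaptive shifting. In the pilot (Principal Findings) it was up to 32% in control against 5.3% with PEER.
- The group exercise is not restricted by quadrant, and Step 2 has content for all four.
- Multiplying d=0.25 by 0.64 to 0.79 gives 0.16 to 0.20, but that assumes no effect outside the maladaptive group, which nothing in the article says. It also treats a figure stated for PEER against control overall as a subgroup effect.
- The stratified analysis in Background is credited with better fall risk assessment. It is not a promise of stratified treatment effects.

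**Conclusion.** The pooled effect should remain the primary estimand. The supportable point is modest: baseline quadrant is collected at T1, is reported to be associated with MVPA and the CDC fall risk score, and governs the tailored content, yet it is not among the named adjusters. The case is clearest for H2.1, where starting quadrant sets whether one or two cut-offs must be crossed; it is weaker for Aim 1, where the T1 outcome already does much of the work. The size of the gain cannot be derived from the article. It depends on how far the arms differ in starting quadrant and how strongly quadrant predicts shifting.

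The Conclusions need a wording change only. An Aim 1 contrast by mismatch status is a trade-off and not a requirement: its SE is roughly 2.1 to 2.5 times the pooled one if the mismatch share is 64% to 79%, and at least twice at any share, before clustering.

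**What to change.** 1. In the H2.1 model for adaptive shifting, add starting quadrant (irrational, incongruent, congruent) as a covariate.
2. Add baseline FRA quadrant to the adjustment list for the Aim 1 mixed models.
3. Reword the Conclusions so that the stated focus is all eligible low-income older adults.
4. Optionally, report an Aim 1 estimate by mismatch status (irrational or incongruent against rational or congruent). Label it exploratory, give its interval, and state its low precision. Any dilution or power figure quoted with it should be marked illustrative.

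The cost is a few words and a few model parameters, with no new data and no change to eligibility. The adjusted odds ratio for H2.1 becomes conditional on starting quadrant, so the percentages shifting in each arm should be shown beside it. Item 4 adds one imprecise contrast per outcome, and a null result there should not be read as evidence of no difference.

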## Abbreviations

BBS: BTrackS Balance Tracking System
CDC: Centers for Disease Control and Prevention
COREQ: Consolidated Criteria for Reporting Qualitative Research
FES-I: Falls Efficacy Scale-International
FOF: fear of falling
FRA: fall risk appraisalGLMM: Generalized Linear Mixed Model
ICC: intraclass correlation
LMM: linear mixed model
LRT: likelihood ratio test
MVPA: moderate to vigorous physical activity
PA: physical activity
PC: peer coach
PD: project director
PEER: Physio-Feedback Exercise Program
PI: principal investigator
RA: research assistant
REDCap: Research Electronic Data Capture
STS: Sit to Stand
TUG: Timed Up and Go
